
### Statistical methods

Primary analyses will be conducted on an intention-to-treat basis using STATA statistical software release (STATA, College Station, TX, USA). Per protocol analysis will also be performed by including all participants who are at least 80% compliant to the exercise (as measured by the number of exercise sessions attended). Initially, descriptive statistics will be computed to compare the intervention and control groups on background variables and baseline measures. Imbalances on prognostic factors between the groups will be adjusted for during analyses. Calculation of QoL scores (SF-36 v2, AQol-6D) will utilise published ‘weightings’ most relevant to this population. Baseline measures and changes in outcome variables over the study period for each study arm will be presented as means (± SD) with 95% confidence intervals. The effect of the intervention on the primary outcome variables will be assessed using negative binomial regression, to account for the non-independence of multiple events for the same participants and to allow for over-dispersion [77]. To account for clustering, the negative binomial regression analysis will be carried out using the generalised linear mixed modelling approach, with observations clustered within retirement villages; village will be modelled as a random effect. Differences between the intervention and control groups on the secondary outcome measures will be examined using linear mixed models with assessment times clustered within individuals and individuals clustered within villages. Village and, where appropriate (as determined by the likelihood ratio tests) individuals, will be modelled as random effects. The secondary outcome variables will be checked for normality prior to analysis and transformed appropriately if necessary. For both primary and secondary outcomes, random effects will be computed utilising robust standard errors. For all outcomes, primary analyses will compare unadjusted differences between the study groups at each follow-up. Supplementary adjusted analyses, with adjustment for potential covariates (baseline values of relevant outcome, age, sex, use of medication, chronic conditions, falls history and other background variables that show imbalances between the intervention and control groups) will also be conducted.

Missing data: where possible, we will obtain endpoint measures from all withdrawals and include all randomised subjects in the final analysis. For participants who are lost to follow- up, missing data will be handled with multiple imputation. As this approach makes an untestable assumption that data are missing at random (that is, missing data can be predicted from the observed data) [77], we will perform sensitivity analysis to evaluate the effect of potential non-random attrition [78]. Sensitivity analyses will employ simulation and will test a range of scenarios assuming plausible arm-specific differences in outcomes for individuals who were lost to follow-up [79].

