### Intervention

#### Dual-task functional power training

Participants residing in the villages assigned to the DT-FPT programme will be asked to train twice a week for 26 weeks. All training will be conducted on-site at each retirement village in small groups (8 to 10 per group), and will be implemented and supervised by accredited exercise physiologists (AEPs), physiotherapists or experienced Certificate IV personal trainers. All trainers involved in the study will be required to attend a ‘train-the-trainers’ workshop and will be provided with a detailed instructor manual that will contain all the necessary information to implement the exercise programme. The delivery of the programme will be standardised through regular quality assurance visits and monthly trainer meetings with the research staff.

The 26-week programme will be divided into an initial 2-week familiarisation (orientation) period, followed by 3 distinct but interrelated 8-week phases termed ‘mesocycles’. Each mesocycle will be further divided into 2-week achievable microcycles that are designed to be progressively more challenging. Each training session is designed to be completed within 45 to 60 minutes and will be divided into 4 components: 1) a warm-up consisting of rhythmic and range of motion exercises, 2) challenging balance and mobility activities, 3) HV-FPT, and 4) a cool-down. Dual-task activities will be incorporated into the challenging balance/mobility and HV-FPT. All programmes will be individualised to the functional capabilities of each participant based on their initial assessment.

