#### Usual care control group

Participants residing in the villages assigned to the control group will receive their usual care from their medical practitioner and community services. They will also be encouraged to adhere to the current guidelines of at least 150 minutes per week of moderate intensity physical activity. They will also receive standardised falls prevention and physical activity advice in the form of booklets (Department of Health: ‘*Don’t fall for it - falls can be prevented’*, and *‘An active way to better health’*) along with generic project newsletters that contain project updates to help minimise attrition over the 18-month duration. There is no evidence that the provision of written falls prevention or physical activity advice alone reduces falls risk [50].

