#### ‘Step down’ maintenance programme and follow-up

A 6-month ‘step down’ maintenance programme will be introduced after the supervised training for the intervention group since previous trials have shown that the benefits of exercise on falls incidence are largely lost after programme cessation [46,47]. The ‘step down’ represents a decrease in the level of free supervised training that will be offered to the participants by the exercise staff who delivered the first 6-months of the programme. Prior to this phase we will liaise with all village managers to discuss strategies as to how they can continue to offer the programme within their village without the intensive intervention of the research staff. Village managers will be provided with a number of potential options as to how they can continue to offer the programme to the residents. To facilitate this transition, participants will be offered 1 weekly 1-hour exercise class led by our trained exercise staff who have completed our ‘train-the-trainers’ workshop. In addition, since one of the goals of the main intervention is to improve gait and muscle function under dual-task conditions, participants will also be encouraged to undertake at least one brisk walking session per week. Within each village, staff/participants will be encouraged to form walking groups. Compliance with the ‘step down’ programme will be monitored by attendance sheets completed by the staff at each village and a diary for recording the walking. After the 6-month ‘step down’ programme, participants will be followed for a further 6 months to establish the long-term residual effects on falls. Participants and staff at the villages will not receive any support or advice during this final 6-month follow-up.

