### Primary outcome measures

The primary outcome will be the number of falls over the 6-, 12-, and 18-month period. The initial comparison of falls outcome between the two groups will be analysed according to the number of falls per person year and the proportion sustaining one or more falls. Subsequent analyses will allow for the non-independence of multiple events for the same participants. Participants will record all falls ((F (fall) or N (no fall)) each day on a monthly falls and adverse events calendar, which will be returned monthly via postage-paid mail. Any participants who do not return the monthly falls calendar will be contacted by telephone by the research staff. When a fall is recorded, a research staff member will administer a standardised questionnaire via telephone to record more specific details of the fall location, cause, injury, treatment and the healthcare utilisation. The fall event data will be coded using the International Classification of Diseases, 10th edition (ICD-10).

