#### Exercise compliance

Compliance with the exercise programme will be assessed by attendance at the supervised exercise sessions and completion of personal exercise cards that will be completed by the participants and checked by the trainers after each session.

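### The supplementary per-protocol analysis selects on exercise attendance in one arm only, so it is open to selection bias that probably favours the programme

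*Protocol article*

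**What the plan says.** The primary analysis is by intention to treat. Statistical methods then adds a second analysis: "Per protocol analysis will also be performed by including all participants who are at least 80% compliant to the exercise", where compliance is taken "as measured by the number of exercise sessions attended". No criterion is given for controls.

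The intervention arm "will be asked to train twice a week for 26 weeks". In the following six months "participants will be offered 1 weekly 1-hour exercise class led by our trained exercise staff"; whether these classes count towards the 80% is not stated. Under Exercise compliance, "Compliance with the exercise programme will be assessed by attendance at the supervised exercise sessions and completion of personal exercise cards". In the other arm, "Participants residing in the villages assigned to the control group will receive their usual care from their medical practitioner and community services", plus written advice and encouragement to be active, but no trial sessions.

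On timing, "The primary outcome will be the number of falls over the 6-, 12-, and 18-month period". The first six months of outcome therefore coincide with the period in which attendance is recorded.

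**The concern.** Sessions attended exist in one arm only. Applying the threshold trims the intervention arm to its high attenders and, on any reading that leaves a comparison, keeps every control. The balance from randomisation is then lost on one side.

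The trimming is also unlikely to be neutral for falls. Frailer people may attend less and fall more, and an injurious fall can itself cause absence. In the second case the outcome removes the person from the intervention group, while a control with the same fall stays in.

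At stake is the supplementary estimate of what the programme does for those who attend it. The Discussion hopes that the results will guide community programmes, and the article does not label this analysis exploratory.

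**Working it through.** The plan gives no figure for the per-protocol set, so there is none to reproduce. Its one relevant risk is the 45% of controls expected to fall over the study (Sample size). All attendance rates below are assumptions, because the article has no data linking attendance to falls.

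**1. How easily a person leaves the set.** 2 sessions × 26 weeks = 52 sessions, and 0.80 × 52 = 41.6. At least 42 must be attended, so 10 may be missed (5 weeks). A single 6-week absence costs 12 sessions and excludes the person. This takes the 26-week supervised programme as the denominator.

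**2. Control risk at 6 months.** With a constant hazard, 45% over 18 months gives 1 − 0.55^(1/3) = 0.18.

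**3. Selection under no effect, 6 months.** Let 70% of non-fallers and a share a of 6-month fallers reach 80% attendance. The proportion of fallers among attenders is 0.18a / (0.18a + 0.82 × 0.70).

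- a = 0.60: 0.108 / 0.682 = 0.158; reduction 1 − 0.158/0.18 = 12%
- a = 0.50: 0.090 / 0.664 = 0.136; reduction 25%
- a = 0.40: 0.072 / 0.646 = 0.111; reduction 38%

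**4. Carried to 18 months.** Suppose that after month 6 everyone has the same constant hazard. A person with no fall by month 6 then stays free of falls to month 18 with probability 0.55^(2/3) = 0.671. With p the 6-month proportion from step 3, the 18-month proportion is 1 − (1 − p) × 0.671, against 0.45 in controls.

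- a = 0.60: 1 − 0.842 × 0.671 = 0.435; reduction 3%
- a = 0.50: 1 − 0.864 × 0.671 = 0.420; reduction 7%
- a = 0.40: 1 − 0.889 × 0.671 = 0.404; reduction 10%

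These figures reflect only the link between early falls and attendance. Lasting differences in frailty would slow the shrinkage.

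**5. Cross-check by another route.** Suppose that a share s of the intervention arm is adherent and that non-adherers have r times the adherers' risk. Under no effect, the risk ratio of adherers to all controls is 1 / (s + (1 − s)r). It is 0.95 for s = 0.8, r = 1.25, and 0.67 for s = 0.5, r = 2. It is 1.00 when r = 1.

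**6. Falls as the only cause of absence.** A no-effect simulation drew fall counts from a gamma-Poisson model (dispersion 1, 45% falling in 18 months). It assumed 85% background attendance and that 10% to 30% of falls cost 2 to 6 weeks of sessions. Applying the limit of 10 missed sessions gave spurious fall rate ratios of 0.92 to 0.65 at 6 months and 0.96 to 0.83 at 18 months. The pattern matches steps 3 and 4: material early, smaller later.

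**The case against.** The strongest reply is that no primary conclusion depends on this analysis. That is right, and it limits the importance of the point. A reader might infer that the trial's main result is biased; the documents do not support that, because the primary analysis is by intention to treat.

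A second reply is that compliance with exercise can only be asked of people who were prescribed it, and that how controls enter a secondary set may be left to an analysis plan. This also has force. A reader might infer that the set contains no controls and the analysis is void. That is the literal wording, but hardly the intention, and the point does not need it. Admitting all controls is what produces the asymmetric comparison.

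Third, the bias is not demonstrated. A reader might infer that the analysis would show benefit even if the programme did nothing. The article has no attendance data, and the artefact vanishes if attendance is unrelated to fall risk. Nor may the 25% be read as applying throughout: it is the 6-month figure, and under the same assumptions it is about 7% at 18 months.

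Fourth, supplementary models adjust for age, sex, medication, chronic conditions, falls history and baseline values. They are not tied to the per-protocol set, though they would cover measured baseline frailty if used there. They cannot undo exclusion caused by a fall after randomisation. The planned sensitivity analyses deal with loss to follow-up, not with non-attendance.

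Finally, an instrumental-variable analysis has weak points of its own here. That is true, and they are counted among the costs of the change.

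**Conclusion.** The point holds in a limited form. The stated rule conditions on behaviour after randomisation that is measured in one arm only and can be altered by the outcome. The resulting comparison probably favours the programme, though this is an expectation and not a certainty.

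Under no true effect and the assumed attendance rates, the spurious reduction in fallers is about 25% at 6 months (12% to 38%) and about 7% at 18 months (3% to 10%) from this mechanism alone. The trial is designed to detect a 40% reduction, so the early artefact could be a sizeable part of an apparent benefit. The size rests on the assumed attendance rates, a constant hazard, and the 52 supervised sessions as denominator. The rule should be changed before analysis; the primary result does not depend on it.

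**What to change.** Estimate the effect of adherence with a complier-average (instrumental variable) analysis on all randomised participants. Use village allocation as the instrument, sessions attended as the exposure (zero for controls by design) and uncertainty at village level, and label the analysis supplementary. Because it starts from the contrast between the arms as randomised, selective attendance alone does not create an effect. Report any result for 80% attenders only as exploratory, or as a description within the intervention arm, and say whether step-down classes count.

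The data are already to be collected, so the cost is modest extra analysis, with three downsides:

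- The interval will be wider, with only about 15 villages carrying the instrument.
- A form must be assumed for the dose-response. If the 80% cut-off is used as the exposure instead, lower attendance must be assumed to have no effect.
- Allocation must act only through attendance. The encouraged walking and walking groups, the social support and the education material may strain this, so it should be stated as a limitation.

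Stating how controls enter the set and calling the analysis exploratory would be cheaper and would remove the ambiguity, but it would leave the selection in place.

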### Sample size

Based on previous research in Australia [71-73], we anticipate that approximately 45% of the usual care control group will experience a fall throughout the study. To detect a 40% reduction in the rate of falls (for example, from 45% to 27%) in the DT-FPT group, we estimate that we will require 118 participants per group (2-tailed, *P* < 0.05 and power of 0.8). This allows for a 15% loss to follow-up due to death or withdrawal from the study. To account for cluster randomisation, we will assume a conservative intra-cluster correlation coefficient of 0.01 [74], giving a design effect of 1.19, assuming approximately 15 to 20 participants are recruited per village. This gives a sample size of 140 per group (280 participants from approximately 15 villages). This sample size will also provide sufficient power (0.9, 2-tailed, *P* < 0.05) to detect significant and clinically meaningful differences in many of the secondary outcome measures. Previous research has shown that 6 months of high-velocity resistance training in older adults can result in a 50% increase in peak muscle power (SD 18%) [20]. This mode of training has also resulted in a reduction in chair rise time of approximately 11% (SD 12%) and stair climbing time of approximately 7% (SD 10%) [20,21]. For the usual care control group, we estimate a mean change of 0 (SD 10%). Thus, to achieve 90% power at *P* < 0.05 (2-tailed), we estimate that 46 participants per group would be required to demonstrate between group differences of this magnitude in these measures. We will also have sufficient numbers to detect the smallest clinically significant differences in other measures of function and the SF-36. Perera *et al*. [75] calculated that a small meaningful change (difference) in function is around 5% (0.05 m/s gait speed) and a substantial change is around 10% (0.10 m/s gait speed). Since we will recruit a cohort at increased risk of falling, we anticipate greater changes based on previous work in healthy community-dwelling older adults (gait speed +7%, chair rise +13%) [21]. We estimate that 32 to 42 participants per group will be needed for a statistical power of 0.9 (2-tailed, *P* < 0.05) to detect differences between the groups of 14 to 25% in gait speed and chair rising time. Using data from a pilot study on dual-task stepping exercise [45], we estimate that we will need 48 participants per group to detect a 20% difference (SD 25%) in dual-task cost at 90% power (2-tailed, *P* < 0.05). For the sub-scales of the SF-36, we anticipate a change of 10 points in the DT + FPT groups with a small age-related change (decrease) in the controls. In various patient groups a 5 to 10% change is regarded as the minimal important difference. We note that the effects of resistance training on SF-36 are mixed, but differences of 15 to 52 points for the various sub-scales have been reported [76].

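### Robust standard errors with only about 15 villages: run as an ordinary Wald z test without a small-sample correction, the 5% falls test would reject about 8 to 8.5% under no effect

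*Protocol article*

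**What the plan says.** Under Statistical methods, the protocol article analyses falls with a negative binomial mixed model in Stata, with village as a random effect, and secondary outcomes with linear mixed models. It then fixes the variance method for all of them: "For both primary and secondary outcomes, random effects will be computed utilising robust standard errors". The section names no bias-corrected sandwich, degrees of freedom, t reference or permutation test.

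Under Sample size, the number of clusters is small: "This gives a sample size of 140 per group (280 participants from approximately 15 villages"). The declared test is "2-tailed, *P* < 0.05 and power of 0.8". Under Randomisation, villages are allocated in blocks of 2 within village-size strata, so the arms hold about 7 and 8 villages.

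**The concern.** Treatment is assigned to villages, so the information about its effect comes from about 15 units, however many residents each contributes. A village-level sandwich estimates the variance from the spread of those units, and with so few two things go wrong. The estimate is biased downward. It is also imprecise, so the test statistic has heavier tails than the normal distribution. If neither is corrected, intervals are too narrow and p-values too small, and a positive primary result would carry a higher false-positive rate than the 5% declared. The model already has a random village effect, so at the planned intra-cluster correlation the sandwich gives little protection and adds its own error.

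**Working it through.** **Inputs from the article.** Two-sided 5% level; 118 per group before clustering (taken as given here); intra-cluster correlation 0.01; 15 to 20 people per village; 280 participants; about 15 villages; 45% of controls falling at least once.

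**The plan's own figures.** Design effect with 20 per village: 1 + (20 − 1) × 0.01 = 1.19. Then 118 × 1.19 = 140.4, the stated 140 per group. At 20 and 15 people per village, 280 participants need 280/20 = 14 and 280/15 = 18.7 villages, so the stated sizes imply 14 to 19 and 15 is in range.

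**Closed form.** Take a difference of village means with k1 and k2 villages, G = k1 + k2. The expected sandwich variance, relative to the true variance, is

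r = [(k1 − 1)/k1² + (k2 − 1)/k2²] / [1/k1 + 1/k2].

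For 7 v 8, r = (0.1224 + 0.1094)/(0.1429 + 0.1250) = 0.865. The usual factor G/(G − 1) = 15/14 raises it to 0.927, so the standard error is √0.927 = 0.963 of the truth. Comparing the statistic with 1.96 amounts to using 1.96 × 0.963 = 1.887 on a t distribution with 13 degrees of freedom (df). The rejection rate is 2 × P(t13 > 1.887) = 8.2%.

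| Villages | With G/(G − 1) | Without |
|---|---|---|
| 14 (7 v 7) | 8.4% | 9.5% |
| 15 (7 v 8) | 8.2% | 9.1% |
| 18 (9 v 9) | 7.5% | 8.3% |
| 19 (9 v 10) | 7.4% | 8.1% |

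**Splitting the cause at 15 villages, with the factor.**
- Small standard error alone: 2 × P(Z > 1.887) = 5.9%.
- Normal reference alone, unbiased variance: 2 × P(t13 > 1.96) = 7.2%.
- Both: 8.2%.
- Same robust error referred to t13: 5.8%.

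**Simulation of the planned model.** Null data, 3,000 trials per setting, random-intercept negative binomial by maximum likelihood, village-level sandwich with G/(G − 1), Wald z. Means were set so that 45% fall at least once. Dispersion (1 or 2), correlations other than 0.01 and the spread of village sizes are assumptions. Monte Carlo error is about 0.5 points.

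| Setting | Robust, z |
|---|---|
| 15 villages, equal sizes, dispersion 1, correlation 0 to 0.05 | 7.7 to 8.5% |
| 15 villages, equal sizes, dispersion 2, correlation 0 to 0.05 | 7.5 to 8.0% |
| 15 villages, size CV 0.4 | 8.5% |
| 15 villages, size CV 0.7 | 9.6% |
| 14 villages, equal sizes | 8.1% |
| 18 villages, equal sizes | 6.7% |
| 19 villages, size CV 0.4 | 8.0% |

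At 15 villages the mean robust error was 0.93 to 0.98 of the true one. With t on 13 df, the robust test rejected 5.2 to 6.3%, or 7.2% at size CV 0.7. With model-based errors and z, it rejected 5.0 to 5.8% at correlation 0.01 but 7.7 to 8.3% at 0.05.

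**Simpler simulation.** A log rate ratio with a village-clustered sandwich and the K/(K − 1) factor (K the number of villages) rejected about 8.5% with 15 to 20 people per village and about 9% with 8 to 30. A t test on village fall rates with villages minus 2 df rejected 4.7 to 4.9%.

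**The case against.** The strongest reply is that the article fixes robust errors but not the reference distribution, and that the reference does most of the damage. What the text itself fixes moves the rate only from 5% to about 5.9%. A degrees-of-freedom rule is commonly left to an analysis plan, and none is shown. This stands as a limit: the 8% figure is conditional on the usual Wald default. It does not dispose of the point. The article actively prescribes an estimator that suits many clusters, and Kenward-Roger corrects the model-based covariance, so adopting it for the continuous outcomes means replacing the sentence rather than adding to it. For falls, a t reference alone still leaves up to 7.2% with very uneven villages.

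It is also fair that model-based errors nearly hold 5% at the planned correlation. They do not if the correlation is 0.05, and with t on 13 df they can be conservative (as low as 2.4%). Dropping the robust errors is therefore not a complete cure.

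A reader might infer three stronger things that the documents do not support:
- **A rate of 10%, or double the nominal level.** That needs very uneven villages and omission of the usual G/(G − 1) factor; the article implies neither.
- **The same inflation in every secondary outcome.** The sentence covers those outcomes, but no linear mixed model was simulated, so no size can be claimed.
- **Invalid secondary analyses because the participant effect may be dropped.** The article does say "Village and, where appropriate (as determined by the likelihood ratio tests) individuals, will be modelled as random effects". Village-clustered robust errors would already allow largely for within-person correlation, and with repeated assessments the test would usually retain the term. No effect on the falls result follows.

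**Conclusion.** The point holds in conditional form. With about 15 villages, robust errors, a normal reference and no small-sample correction, the two-sided 5% falls test has a false-positive rate of about 8 to 8.5%, or 1.6 to 1.7 times nominal. It is about 7 to 8% at 18 to 19 villages and about 9 to 9.6% with very uneven village sizes. The normal reference and the lack of a correction are assumptions about how the stated method would usually be run. Dispersion and size variation are also assumed, but the result changes little with dispersion from 1 to 2. The standard error is only about 2 to 7% too small on average. The main cause is treating a variance estimated from about 15 units as if it were known.

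**What to change.** Replace the robust-error sentence before any unblinded analysis.

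- **Falls:** keep the negative binomial mixed model for the estimate. Take the confidence interval and p-value from one named small-sample method: either a bias-corrected village-level variance with a t reference on villages minus 2 df, or a t test on village fall rates.
- **Continuous outcomes:** use REML with Kenward-Roger or Satterthwaite degrees of freedom instead of uncorrected robust errors.

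The change needs analysis wording and a few lines of code, and leaves design and data collection as they are. For a given standard error, a t reference on 13 df widens the interval by 2.160/1.960 = 1.10, about 10%. In information terms, [(2.160 + 0.870)/(1.960 + 0.842)]² = 1.17, so about 17% more information is needed for the same 80% power. That is the real price of having few villages, and it should be stated alongside the sample size.

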#### Randomisation

Randomisation will be performed by cluster (village) to avoid any potential contamination and facilitate logistical arrangement. Each village will be given an ID number and group assignment by blocks of 2, stratified by village size (<75 or ≥ 75 residents), will be performed by a researcher not involved in the study using computer-generated random numbers (Microsoft Excel, Microsoft Corp., Redmond, WA, USA). A flow diagram of the study protocol is outlined in Figure 1.

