### Secondary outcome measures

The secondary outcome measures to be assessed at baseline, 6, 12, and 18 months (unless stated) will include: changes in lower limb functional muscle strength and power, isometric knee extensor, dorsi-flexor and hand grip strength, dynamic balance and reaction time, gait, Instrumental Activities of Daily Living (IADL), quality of life, cognitive function and falls- related self-efficacy (Table 2).

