#### Lifestyle and medical history

A lifestyle questionnaire will be used to obtain detailed information on the participant’s ethnic and education background, employment history/status, medical history, previous history of any falls and fractures, family history of osteoporosis, current medication and dietary supplement use, smoking status, weekly television viewing and sitting time, and sun exposure habits.

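### The primary analyses are fixed as unadjusted, without the village-size stratum or the baseline data, and another sentence lets the primary model be read two ways

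*Protocol article*

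**What the plan says.** All references are to the protocol article.

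- **Randomisation.** Villages are allocated in strata: "group assignment by blocks of 2, stratified by village size (<75 or ≥ 75 residents".
- **Statistical methods, primary analysis.** "For all outcomes, primary analyses will compare unadjusted differences between the study groups at each follow-up". Falls are analysed by negative binomial mixed regression and secondary outcomes by linear mixed models. Village is a random effect; the size stratum is not mentioned.
- **Statistical methods, supplementary analysis.** "Supplementary adjusted analyses, with adjustment for potential covariates (baseline values of relevant outcome, age, sex, use of medication, chronic conditions, falls history", together with "other background variables that show imbalances between the intervention and control groups". Village size is not named here either.
- **Statistical methods, earlier sentence.** After the descriptive comparison of the groups: "Imbalances on prognostic factors between the groups will be adjusted for during analyses". Nothing limits this to the supplementary analyses.
- **Data available before allocation.** For secondary outcomes: "The secondary outcome measures to be assessed at baseline, 6, 12, and 18 months (unless stated". Under Lifestyle and medical history, the questionnaire records "previous history of any falls and fractures". Table 1 scores whether there was at least one fall in the past year. Under Allocation concealment and blinding, villages are allocated only after baseline testing is complete.

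**The concern.** Stratifying on village size removes chance differences in size between the arms. The standard error reflects that only if size is in the model. A village random effect does not do this: variation due to size stays in the between-village error.

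Baseline values and falls history are natural predictors of the outcomes, are collected before allocation and so cannot be affected by it. With about 15 villages, seven or eight per arm, stratifying on size does nothing to balance them. Leaving them out of the headline model gives up precision and leaves any chance difference in the headline estimate.

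The imbalance sentence adds a separate difficulty. If a prognostic factor looks imbalanced, one sentence calls for adjustment and another says the primary comparison is unadjusted. Whatever threshold is used, a covariate set chosen by observed imbalance depends on the data.

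This is not detail left to a later plan, because the article positively fixes the primary analysis as unadjusted.

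**Working it through.** **Inputs from the Sample size section.** ICC 0.01, design effect 1.19, 15 to 20 participants per village, 140 per group, about 15 villages. The design effect reproduces at 20 per village: 1 + (20 − 1) × 0.01 = 1.19, and 118 × 1.19 = 140.4. How 118 was reached does not bear on this point.

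**Inputs the article does not give.** It states neither the baseline–follow-up correlation r nor the share of between-village variance due to size. Both are assumed below over a range.

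**1. Omitting the stratum.** Village means were simulated for 16 villages (8 per stratum, blocks of 2, 17.5 participants each) with total variance 1. If size explains a fraction f of the between-village variance of 0.01, the strata differ by 2√(0.01f). The remaining SD of a village mean is √(0.99/17.5 + 0.01(1 − f)). The strata therefore differ by 0.40, 0.57 and 0.84 of that SD at f = 0.25, 0.5 and 1. The treatment effect was set at 1.5 of that SD, and two-sided 5% t-tests were run with and without the stratum.

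| f | Type I error, unadjusted | Type I error, with stratum | Power, unadjusted | Power, with stratum |
|---|---|---|---|---|
| 0.25 | 0.045 | 0.049 | 78.3% | 79.1% |
| 0.50 | 0.042 | 0.050 | 76.9% | 79.1% |
| 1.00 | 0.033 | 0.049 | 73.8% | 79.3% |

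The loss is about 1, 2 and 5 points. With no size effect at all, power was 79.7% unadjusted and 79.2% with the stratum, so an unneeded stratum term costs about half a point.

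**2. Omitting the baseline value of a continuous secondary outcome.** The gain depends on what the unadjusted comparison is:

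- Against a comparison of follow-up values only, the factor on individual-level variance is 1 − r².
- Against a comparison of changes, it is (1 − r²) / (2(1 − r)) = (1 + r)/2.

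For a comparison with 80% power before adjustment, power afterwards is Φ(2.80/√factor − 1.96), where 2.80 = 1.96 + 0.84.

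| Assumed r | Factor, follow-up only | Power | Factor, change scores | Power |
|---|---|---|---|---|
| 0.5 | 0.75 | 90% | 0.75 | 90% |
| 0.7 | 0.51 | 98% | 0.85 | 86% |

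At r = 0.3 the follow-up-only factor is 0.91 and power about 84%.

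**3. Falls.** Neither factor applies to the negative binomial model. There is no baseline calendar count; the counterpart is falls history, and the article gives nothing from which to compute its gain.

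**4. The two sentences side by side.** "Imbalances on prognostic factors between the groups will be adjusted for during analyses" covers analyses in general, while "For all outcomes, primary analyses will compare unadjusted differences between the study groups at each follow-up" excludes adjustment from the primary ones. They agree only if the first is confined to the supplementary analyses, which the text does not say.

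**The case against.** An unadjusted primary analysis with named adjusted analyses behind it is an unbiased, pre-specified choice; reversing the order is an argument about efficiency. That stands, and it limits the point to an improvement rather than an error of validity.

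Several stronger readings are tempting and are not supported:

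- **A flat contradiction with two rival primary results.** Only one analysis is labelled primary, and the imbalance sentence is naturally carried out by the supplementary step, which also names imbalanced variables. What remains is wording that permits a second reading.
- **A gain like doubling the sample.** The factor 0.51 at r = 0.7 would suggest this, but only for continuous secondary outcomes and only if the unadjusted model ignores baseline. Baseline is one of four testing sessions, the Secondary outcome measures section describes changes, and some of the power figures rest on percentage change. If baseline is used through change, the gain at r = 0.7 equals about 18% more participants (1/0.85 = 1.18). The text leaves both readings open.
- **High r inferred from the quoted test-retest reliabilities.** The figures of 0.84 to 0.98 describe repeatability, not correlation over 6 to 18 months in people at risk of falling, some of whom are being trained.
- **Serious chance imbalance as the likely result.** At the plan's design effect, 140 per arm is worth 140/1.19 = 117.6 independent participants. The SD of a baseline mean difference is then √(2/117.6) = 0.13 SD, and a difference beyond 0.25 SD has roughly a 5 to 6% chance. A higher ICC for baseline measures would raise this, but the article does not give one.
- **A past-year falls count to adjust for.** Table 1 scores only whether at least one fall occurred, and the questionnaire records falls history without stating a 12-month count.

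**Conclusion.** The point holds as a worthwhile improvement. The article fixes an unadjusted primary analysis for every outcome, names the stratification factor in no model, and keeps baseline values and falls history for supplementary analyses. Its imbalance sentence leaves the primary model open to two readings and makes covariates depend on observed data.

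A reader might infer a raised false-positive rate from leaving out the stratum. The check shows the opposite: simulated type I error was 0.033 to 0.045, below the nominal 0.05. The stratum cost is small, and the loss of about 5 points requires size to explain all between-village variance. The potential gain from baseline values in continuous secondary outcomes is larger, but its size depends on the assumed r and on whether the linear mixed model already uses baseline. No gain has been quantified for falls, the primary outcome.

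The stratum results assume 16 equal-sized villages split evenly between strata, and a test on village means rather than the planned mixed model. The baseline factors describe individual-level variance only.

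**What to change.** Before analysis, amend Statistical methods as follows:

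1. **Falls (primary model).** Include the village-size stratum and falls history as collected at entry, at least the indicator for one or more falls in the past year. Use a count only if one is confirmed as recorded.
2. **Secondary outcomes (primary model).** Include the village-size stratum and the baseline value of that outcome.
3. **Unadjusted comparisons.** Report them as supplementary.
4. **Imbalance rules.** Delete both: the general sentence, and the clause in the supplementary list that admits variables showing imbalance. The named covariates in that list can stay as a fixed supplementary set.

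The cost is wording and one or two degrees of freedom per model. No new data are needed, because these items are collected before villages are allocated.
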